### Participants and recruitment

Participants are being recruited from antenatal clinics across three large metropolitan hospitals in Greater Western Sydney, Australia. Information about the study is provided to all pregnant women attending their first antenatal visit (booking visit). At all Australian antenatal clinics the first booking visit is attended by midwives. While waiting to see the midwife, pregnant women are invited to participate by an independent recruiter (dental assistant). Women are eligible for recruitment (inclusion criteria): if they are more than 18 years of age; do not have cardiac disease that would warrant the need of antibiotics for dental treatment; have not received dental treatment in the current pregnancy; have a single pregnancy of more than 12 and less than 20 weeks of gestational age; do not have any known foetal anomalies or other risk factors (including history of preterm birth) that would place the pregnancy at risk of complications; and are able to attend regularly for dental treatment if required. Informed written consent is obtained by the dental assistant from pregnant women who meet the study inclusion criteria.

A self-administered pre-questionnaire is then provided to obtain baseline demographic data, dental/medical aspects of the women’s health (such as uptake of dental services, quality of oral health) and pre-test oral health knowledge. In addition, the Oral Health Impact Profile-14 (OHIP-14) questionnaire will also be administered. The OHIP-14 is a subjective measure of oral health that has been used extensively and found to be a precise, valid and reliable instrument (α=0.88) [27, 28]. It contains 14 questions assessed on a 5-point Likert scale and the total scores range from 0–56 with higher scores indicating poorer oral health. The OHIP-14 assists in validation and determining the sensitivity and specificity of the midwifery oral assessment tool by representing the ‘gold standard’ for identifying participants at risk of having oral health problems. Participants from non-English speaking backgrounds are provided, if required, interpreter services and translated oral health promotional materials.

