### Randomisation

Following consent and baseline data collection participants are allocated to the groups using block randomisation. This form of randomisation is recommended for large trials [29] and has been used in a number of recent trials in this research area [21]. A permuted block randomisation scheme with a random mixture of block sizes is used to set the allocation order, stratifying participants by hospital and presence of a dental problem. Block randomisation ensures that the number of participants in each arm of the trial will be evenly balanced [29]. Randomisation of participants is accomplished centrally using an independent computerised service which is accessed via the telephone at the time of recruitment.

Group allocation (IG1, IG2, CG) is represented by coloured stickers concealed in serially numbered opaque randomisation envelopes. After recruitment, baseline data collection and randomisation via telephone, the dental assistant hands over the randomisation envelope to the pregnant women, who then gives it to the midwife. All midwives at each of the hospitals are aware of which group each coloured sticker represents. To maintain allocation concealment and minimise selection bias the dental assistants are unaware of the colour codes and block sizes used for randomisation. In addition, the study investigators are blinded to group allocation. Due to the randomisation method, pregnant women attending on the same day receive different interventions.

To minimise any distress among pregnant women and maintain equipoise [30], oral health promotion material are provided via the dental assistant at recruitment to all trial participants. Women who refuse to participate are also provided with oral health promotional material. It is also possible that women attending the antenatal clinic on the same day might interact with each other which can lead to potential contamination (estimated at <5%) in the study. We are adjusting for this contamination during analysis [31] and have also included an item in the post questionaire asking if they have discussed their particpation in the study with other women attending the antenatal clinic at the same time. Analysis is being undertaken excluding such women.

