##### Dental intervention

At the first appointment all the women undergo an initial dental oral assessment that includes medical history, followed by oral mucosal tissue examination, periodontal examination, dental caries examination and denture evaluation. A provisional diagnosis and treatment plan is made for those women having oral health problems. Once the consent for treatment is obtained, subsequent appointments are made in the second trimester to complete all the urgent treatment for women having dental problems. The second trimester (13–27 weeks) is considered a safe period to carry out necessary dental treatment^10^. The completion of treatment will take 1 to 3 additional visits depending on the treatment plan. Women having complex treatment needs such as root canal treatment are referred to the specialist for follow up care and are excluded from the study. After each examination participants are provided oral health education including oral hygiene instructions, brushing and flossing instructions and dietary counselling.

All women in the control group, intervention group 1 and group 2 (whether or not at risk of dental problems) undergo a final dental oral assessment by the study dentists at 28–38 week gestation period, the end point of this study. This examination is similar to the initial dental oral assessment and includes a detailed clinical examination. All women receive reminder cards from midwives followed up by telephone calls from the study administrative assistant to attend their final dental oral assessment. Pregnant women in the control group identified with a dental problem are referred to dental services after pregnancy. A post questionnaire having similar items to the pre questionnaire (demographic data, dental/medical aspects of the women’s health such as uptake of dental services, quality of oral health and post-test oral health knowledge), is administered to all women between 28–32 weeks. Contact details of private dentists who were consulted during pregnancy are also sought in the post questionnaire. The following methods are used to administer the post questionnaires: via the dental assistant/receptionist in the antenatal waiting room, via the midwife during the antenatal visit, over the phone when the final dental appointments are being made and via the study dentists at the final dental appointment.

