*Birth outcomes*: Gestational age at birth and birth weight is obtained from the ObstetriX data system (ODS) [41] which is a reliable data source (Kappa =0.75) using data items/definitions from the NSW Perinatal Data Collection (population based surveillance system covering all births in NSW public/private hospitals). Data from ODS is accessed using the women’s medical record numbers and date of birth (collected at recruitment) through local data custodians.*Specificity and sensitivity of midwifery assessment:* To further confirm the practicality of this tool, the midwifery oral assessment tool (2 items) will be compared with two gold standard measures- the OHIP-14 questionnaire (completed at the time of recruitment: pre-questionnaire) in IG1 and IG2 and the initial dental oral assessment conducted by the two study dentists in IG2. This will allow for women with and without oral health problems (the proportion of true and false positives and the proportion of true and positive negatives) to be identified. The OHIP-14 questionnaire has been used as the gold standard in previous studies to validate oral assessment tools [36, 42]. The two study dentists are trained to follow a standardised dental protocol during pregnancy. Adherence to the protocol is being evaluated by assessing the returned checklist.

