### Data analysis

Per-protocol and intention-to-treat analysis will be conducted by staff blinded to the group allocation. Missing data will be coded in the database structure and handled using an appropriate method. Demographic data will be analysed using descriptive statistics. All variables will be examined for normality and appropriate data transformations will be applied. Potential confounders (income, pre-existing oral health conditions, and others) and the impact of the MIOH/MIOH-DS intervention will be examined using univariate and multivariate methods. Regression analysis that take into account the variables of interests to the outcome will be performed. Some of the variables will be considered as exerting fixed effects (e.g. the number of patient groups) while others as random effects e.g. oral health knowledge. The regression models will also include a hospital variable (1–3). Analysis will be conducted for each hospital clinic and if no differences are found, data will be pooled. Pearson’s Chi-square test will be used to analyse the proportion of pregnant women accessing dental services. Oral health status and knowledge outcomes will be analysed using Analysis of Variance and post-hoc procedures. The effectiveness of the oral health education program will be assessed using dependent t-tests.

The sensitivity and specificity of the oral assessment tool using the OHIP-14 as the gold standard will be calculated using odds ratios. For this analysis the total scores using the midwifery oral assessment tool for participants in IG1 and IG2 will be dichotomised as 0=0 (no risk) and 1 to 2=1 (at risk). The total scores for participants using the OHIP-14 in IG1 & 2 will also be dichotomised using the median split as described by Locker et al. [42]. Subjects with an OHIP-14 score of 0–7 will be scored 0 (no risk) and 8–56 a score of 1 (at risk). Sensitivity and specificity will also be calculated using the initial dental oral assessment in IG2 as the gold standard. Analysis of proportions using chi square procedures (two tailed) and confidence intervals will be undertaken to determine sensitivity (true positives), specificity (true negatives), false positives, false negatives, negative and positive predictive values [46].

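### The arm comparison of oral health is assigned to plain ANOVA, although two baseline oral-health scores taken before randomisation in every arm could serve as covariates at no cost

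*Protocol article*

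**What the plan says.** All references are to the protocol article.

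- **When OHIP-14 is taken.** Participants and recruitment describes the pre-questionnaire and then adds: "In addition, the Oral Health Impact Profile-14 (OHIP-14) questionnaire will also be administered". The score runs from 0 to 56, with a quoted alpha of 0.88. Randomisation states: "Following consent and baseline data collection participants are allocated to the groups using block randomisation". All three arms therefore have the score before allocation.
- **What it is for.** "The OHIP-14 assists in validation and determining the sensitivity and specificity of the midwifery oral assessment tool". Outcome measures and Data analysis confine this use to the two intervention arms: "the OHIP-14 questionnaire (completed at the time of recruitment: pre-questionnaire) in IG1 and IG2". No use of the control-arm scores is stated.
- **The other baseline score.** Outcome measures places a 1–5 self-rating of teeth and mouth in both the pre and post questionnaires, for all arms.
- **Clinical indices.** Bleeding, attachment loss, plaque and DMFT are measured at the dental assessments. The initial assessment belongs to IG2 only (Intervention group 2 and Dental intervention); every arm has the final one.
- **Stratification.** Allocation is stratified by hospital and by whether a dental problem is present.
- **Analysis.** "Oral health status and knowledge outcomes will be analysed using Analysis of Variance and post-hoc procedures". The same section lists "Potential confounders (income, pre-existing oral health conditions, and others" for univariate and multivariate examination, and puts hospital in the regression models.

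**The concern.** Improved oral health is one of the three parts of the primary hypothesis. The method named for comparing it across arms carries no baseline term. The passage on confounders does mention prior oral health, but leaves open how it is measured.

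The most natural baseline, the clinical index itself, cannot be used. It is missing by design in IG1 and the control group, and in IG2 it is recorded after allocation. That leaves OHIP-14, the self-rating and the dental-problem stratum. The article gives OHIP-14 a different job, in two arms only, and gives the baseline self-rating no stated role in the analysis of clinical outcomes. What is at stake is precision that could be had from data already being collected.

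**Working it through.** **1. The plan's own sample sizes.** Inputs from Sample size: two-sided alpha 0.017 (z = 2.387), power 80% (z = 0.842), uptake 30% against 50%, bleeding 50% against 20%.

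Formula: n = [z₁√(2p̄(1−p̄)) + z₂√(p₁(1−p₁) + p₂(1−p₂))]² / (p₁−p₂)².

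- Uptake: (2.387 × 0.6928 + 0.842 × 0.6782)² / 0.04 = 123.7, so 124.
- Bleeding: (2.387 × 0.6745 + 0.842 × 0.6403)² / 0.09 = 51.3, so 52.
- With 40% combined loss: 124/0.6 = 206.7, so 207; 52/0.6 = 86.7, so 87.

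All four match the article. None depends on baseline adjustment.

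**2. Which oral-health measures exist at baseline in each arm.**

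| Measure | CG | IG1 | IG2 | Before allocation |
|---|---|---|---|---|
| Clinical indices | no | no | yes | no |
| OHIP-14 | yes | yes | yes | yes |
| 1–5 self-rating | yes | yes | yes | yes |
| Dental-problem stratum | yes | yes | yes | yes |

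Only the last three can serve as covariates in a three-arm comparison.

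**3. Gain from adjustment, continuous outcome.** Let r be the correlation between the baseline score and the final outcome. The article gives no value, so r is an assumption shown as a range. Residual variance is multiplied by 1 − r², and the equivalent number per group is 124/(1 − r²).

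Unadjusted, the difference detectable with 124 per group is (2.387 + 0.842) × √(2/124) = 0.410 SD. Adjusted, it is 0.410 × √(1 − r²).

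| r | Variance reduction | Equivalent n per group | Detectable difference (SD) | Power at 0.410 SD |
|---|---|---|---|---|
| 0 | 0% | 124 | 0.410 | 80.0% |
| 0.1 | 1% | 125 | 0.408 | 80.5% |
| 0.2 | 4% | 129 | 0.402 | 81.8% |
| 0.3 | 9% | 136 | 0.391 | 84.1% |
| 0.4 | 16% | 148 | 0.376 | 87.2% |

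**4. Limits of the table.** It treats r as the only source of gain. If the dental-problem stratum is in the model and already explains part of the outcome, OHIP-14 adds only what remains. The factor 1 − r² belongs to linear models and does not carry over directly to bleeding analysed as a proportion.

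**5. Is precision short for bleeding?** With 124 per group and no adjustment, power is 99.7% for 50% against 20%, the reading that reproduces 52. Sample size also speaks of a 30% reduction. Read as relative (50% against 35%), power with 124 per group is about 50%.

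**The case against.** The strongest reply is that the article already foresees adjusted regression. The confounder list is open and includes prior oral health, and an exact covariate list is commonly left to an analysis plan, which is not shown here. This stands in part. A reader might infer that OHIP-14 is excluded as a covariate, and the text does not support that: it is neither named nor ruled out. What remains is that the article does name a method for oral health status, and that method has no baseline term.

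Three other stronger readings are tempting.

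- **That OHIP-14 is never asked again.** The listed follow-up content omits it, and it is introduced as an addition to the pre-questionnaire. But the article also says: "A post questionnaire having similar items to the pre questionnaire". The list is condensed and the questionnaires are not shown, so this is undecided. Making OHIP-14 a follow-up outcome would be a design preference, in a trial already recruiting.
- **That the primary oral-health hypothesis rests on one coarse item.** It does not. Sample size expresses oral health status as gingival bleeding, and the 1–5 item is a separately listed outcome.
- **That the comparison is biased.** Leaving out a baseline covariate does not bias a randomised comparison.

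It is also fair to say that the gain is modest. It is small below r of about 0.3, the stratum may absorb part of it, and on the 50% against 20% reading bleeding has power to spare. All of this stands and limits the point to efficiency and clarity. It does not count against a change that needs no new data.

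**Conclusion.** The point holds as a free improvement in method. The article assigns oral health status to plain ANOVA and ties its mention of prior oral health to no measure, although two baseline scores and a stratification factor are available in all arms.

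For a continuous outcome, and assuming r between 0.2 and 0.4, residual variance falls by about 4 to 16%, so that 124 per group act like 129 to 148. That is an upper figure for what OHIP-14 adds once the stratum is in the model. The correlation is assumed throughout; nothing in the article supports a particular value. No stated sample size is wrong on this account, and the unadjusted comparison remains valid.

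**What to change.** In Data analysis, replace plain ANOVA for the arm comparison of final oral health status and final self-rated oral health with ANCOVA or regression, using logistic regression for bleeding as a binary outcome. The model should contain arm, baseline OHIP-14, the baseline 1–5 self-rating, hospital and the dental-problem stratum. State that these baseline scores are what the confounder sentence means by prior oral health. The pairwise arm comparisons can be taken from this model.

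The cost is a change of analysis wording. The scores are already collected from every woman before allocation, so no visit, item or participant is added. The wording should be fixed before outcome data are examined by arm, so that the covariates are not chosen after seeing results.

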### Sample size

Sample size estimation is calculated on the outcome measure uptake of dental services using the assumption that 30% of pregnant women in the control group will access dental services during pregnancy (based on our survey [23] and existing Australian studies [10, 43, 44]. We expect the MIOH (IG1) and MIOH-DS service (IG2) will improve the uptake of dental services. The MIOH intervention is considered successful if at least 50% of the pregnant women in IG1 and IG2 will access dental services during pregnancy, a difference of 20% between the groups. To detect a difference of at least 20% between the groups with a two-sided test of proportions, alpha of 0.017 (three comparisons 0.05/3), and 80% power we determine using a statistical software that we require at least 124 patients in each group. Taking into account 10% attrition (refusal after randomisation-based on the results of our pilot survey) and 30 % loss at the endpoint (based on trials in this area - range 2-30%) [21] we will need to recruit 207 participants in each group.

Sample size was also calculated on the outcome measure oral health status using the assumption that 50% of pregnant women in the control group will have gingival bleeding (based on trials in this area) [21]. A 30% improvement in oral health status is expected in IG1 and IG2 (30% reduction in gingival bleeding). To detect a difference of at least 30% between the groups with a two-sided test of proportions, alpha of 0.017, and 80% power we determine using statistical software [45] that we require at least 52 patients in each group. Taking into account 10% attrition and 30 % loss at the endpoint we will need to recruit 87 participants in each group. Based on these estimations we will require a total of 621 participants for the trial (207 in each group). Interim analyses will be used to re-check the sample size after the first 100 women are recruited.

### Data analysis

Per-protocol and intention-to-treat analysis will be conducted by staff blinded to the group allocation. Missing data will be coded in the database structure and handled using an appropriate method. Demographic data will be analysed using descriptive statistics. All variables will be examined for normality and appropriate data transformations will be applied. Potential confounders (income, pre-existing oral health conditions, and others) and the impact of the MIOH/MIOH-DS intervention will be examined using univariate and multivariate methods. Regression analysis that take into account the variables of interests to the outcome will be performed. Some of the variables will be considered as exerting fixed effects (e.g. the number of patient groups) while others as random effects e.g. oral health knowledge. The regression models will also include a hospital variable (1–3). Analysis will be conducted for each hospital clinic and if no differences are found, data will be pooled. Pearson’s Chi-square test will be used to analyse the proportion of pregnant women accessing dental services. Oral health status and knowledge outcomes will be analysed using Analysis of Variance and post-hoc procedures. The effectiveness of the oral health education program will be assessed using dependent t-tests.

The sensitivity and specificity of the oral assessment tool using the OHIP-14 as the gold standard will be calculated using odds ratios. For this analysis the total scores using the midwifery oral assessment tool for participants in IG1 and IG2 will be dichotomised as 0=0 (no risk) and 1 to 2=1 (at risk). The total scores for participants using the OHIP-14 in IG1 & 2 will also be dichotomised using the median split as described by Locker et al. [42]. Subjects with an OHIP-14 score of 0–7 will be scored 0 (no risk) and 8–56 a score of 1 (at risk). Sensitivity and specificity will also be calculated using the initial dental oral assessment in IG2 as the gold standard. Analysis of proportions using chi square procedures (two tailed) and confidence intervals will be undertaken to determine sensitivity (true positives), specificity (true negatives), false positives, false negatives, negative and positive predictive values [46].

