##### Education for midwives and dentists

Prior to the commencement of the trial all midwives from participating hospitals undertake the specific oral health education program endorsed by the Australian College of Midwives [18]. Midwives have to complete the program and competency assessment to ensure that they have adequate knowledge of oral health and are competent to undertake an oral visual inspection. Prior to the trial the two study dentists employed for the study participate in a two hour education workshop where they are trained by an experienced dental clinician to follow a standardised dental protocol during pregnancy. Training is also provided on the use of the oral health status measures. Inter-rater reliability testing of the dentists’ oral health assessments will be examined using 10 mock oral assessments.

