**Detailed design of MIOH-DS trial.**

### Outcome measures

The following outcome measures—estimates of uptake of dental services, oral health knowledge, quality of oral health, oral health status and birth outcomes are proposed for this trial:

*An estimate of the uptake of dental services* will be obtained from the following sources: the returned checklist; the database of the study dental clinics; data from the post questionnaire, following up all referrals by midwives and at the final dental oral assessment period; contacting private/health fund dentists used by the women (contact details obtained from the post questionnaire and returned checklist).*Oral Health Knowledge* will be assessed using a pre-test and post-test questionnaire (tested in the pilot study) [19] and administered to pregnant women at the recruitment and final dental oral assessment period respectively.*Quality of oral health* will be assessed using the following validated item [37] to be included in the pre and post questionnaire: ‘On a scale of 1–5 where 1= poor and 5=excellent, How would you describe the health of your teeth and mouth?*Oral health status* will be assessed using several measures—gingival inflammation and bleeding, clinical attachment loss, level of plaque and dental caries*.* These measures are to be used at both the dental oral assessments: –Gingival inflammation and bleeding is assessed using The Sulcus Bleeding Index [38] and is used to measure the degree of inflammation and bleeding in the gums;–Clinical Attachment Loss (CAL), measures the degree of CAL (periodontal pocket depth, gingival recession and calculus) and is assessed using a calibrated periodontal probe [39];–Level of plaque is measured using The Approximal Plaque Index [38].–Dental caries will be determined by the Decayed, Missing, Filled Teeth (DMFT) Index [40]. The DMFT index is used to monitor the changes in the various components. If the intervention is successful decayed teeth will have been filled or removed.

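### Oral health knowledge is named as a random effect although it is a primary-hypothesis outcome score, and the ANOVA named for it specifies no adjustment for the pre-test

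*Protocol article*

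**What the plan says.** The Primary hypothesis section lists three targets against control: uptake of dental services, oral health, and a 30% gain in knowledge. Under Outcome measures, knowledge "will be assessed using a pre-test and post-test questionnaire". The Participants and recruitment section has women complete a questionnaire after consent that collects "baseline demographic data, dental/medical aspects of the women’s health (such as uptake of dental services, quality of oral health) and pre-test oral health knowledge". The Randomisation section places this baseline collection before allocation, which is stratified by hospital and by presence of a dental problem.

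The Data analysis section then makes four statements that bear on knowledge:

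- Regression models will treat some variables as fixed effects, "while others as random effects e.g. oral health knowledge".
- For the comparison between arms it says: "Oral health status and knowledge outcomes will be analysed using Analysis of Variance and post-hoc procedures".
- A separate sentence introduces paired testing: "The effectiveness of the oral health education program will be assessed using dependent t-tests".
- On adjustment for other variables it says: "Potential confounders (income, pre-existing oral health conditions, and others) and the impact of the MIOH/MIOH-DS intervention will be examined using univariate and multivariate methods". A hospital variable is also to be included.

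**The concern.** A random effect represents a grouping factor whose levels are treated as a sample, such as hospital, midwife or woman. A knowledge score is a measurement. In this trial it is also an outcome, so it belongs on the left-hand side of its own model. It is the only example the article gives of a random effect, so an analyst who follows the text literally has nothing sound to fit.

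Two lesser matters sit beside this. The between-arm method named for knowledge gives the pre-test no role as a covariate, although the pre-test is already in hand. And the purpose of the dependent t-tests is unclear. If they are run on the women's scores, they are within-arm comparisons and could be misread as evidence that the intervention works. What is at stake is the correctness and precision of one of the three primary-hypothesis comparisons.

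**Working it through.** **1. The roles given to knowledge, side by side.**

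| Place | Role |
|---|---|
| Primary hypothesis | outcome, compared with control |
| Outcome measures | questionnaire score, before and after |
| Data analysis, ANOVA sentence | dependent variable |
| Data analysis, regression sentence | random effect |

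The first three agree and the fourth does not fit them. Taken literally, each distinct score would become an unordered cluster with its own random intercept. That discards the order of the scores and, in a model for knowledge, groups women by the outcome itself. A random slope on knowledge would need a stated grouping factor, and none is given.

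**2. The plan's own figure.** No sample size is stated for knowledge. The uptake figure supplies the group size, alpha and power used below: "alpha of 0.017 (three comparisons 0.05/3), and 80% power we determine using a statistical software that we require at least 124 patients". With 30% against 50%, z(0.9915) = 2.387 and z(0.80) = 0.842:

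n = [2.387 × √(2 × 0.4 × 0.6) + 0.842 × √(0.21 + 0.25)]² / 0.20² = 123.7, so 124 per group.

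Allowing 40% loss, 124 / 0.6 = 206.7, so 207. Both figures reproduce, and this point does not affect them.

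**3. Precision for knowledge.** Let r be the correlation between pre-test and post-test scores. The article gives none, so 0.3, 0.5 and 0.7 are assumptions. Relative to a post-score ANOVA (variance 1), a change-score analysis has variance 2(1 − r) and ANCOVA has 1 − r². The group size giving the same precision as 124 under ANOVA is 124 × the ratio, rounded up. The detectable difference in SD units at alpha 0.017 and 80% power is 3.228 × √(2 × ratio / 124).

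| r | Change-score ratio | ANCOVA ratio | Equivalent n, ANCOVA | Detectable, ANOVA | Detectable, ANCOVA |
|---|---|---|---|---|---|
| 0.3 | 1.40 | 0.91 | 113 | 0.41 | 0.39 |
| 0.5 | 1.00 | 0.75 | 93 | 0.41 | 0.36 |
| 0.7 | 0.60 | 0.51 | 64 | 0.41 | 0.29 |

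ANCOVA is never less precise than the change score, because 2(1 − r) − (1 − r²) = (1 − r)².

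**4. Validity of the unadjusted ANOVA.** A simulation used 124 per arm, r = 0.5, 4,000 runs and the overall F test at 0.05. The type I error was 0.058 for ANOVA and 0.055 for ANCOVA, with a simulation standard error of about 0.0035. The F test is exact for the normal data simulated, so the small excess is chance. With a 0.3 SD effect in both intervention arms, power was 0.68 for ANOVA and 0.80 for ANCOVA.

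**5. What a within-arm paired test shows.** Suppose all arms gain an equal 0.2 SD (assumed), so there is no intervention effect. In one arm of 124 the standard error of the mean change is √(2(1 − r)/124), and the chance of significance at two-sided 0.05 is Φ(0.2/SE − 1.96). This is 0.47, 0.61 and 0.82 for r = 0.3, 0.5 and 0.7. A significant within-arm gain therefore says little about a difference from control.

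**The case against.** The random-effect wording has no good defence. The authors may have meant only that knowledge is a measured variable, but that is not what a random effect is.

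On the rest the other side is strong:

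- **A reader might infer that the ANOVA is invalid.** It is not. Randomisation protects an unadjusted comparison of post-test scores, and only precision is lost. The text does not say which score enters, so a change-score or repeated-measures ANOVA is also possible. The article plans multivariate methods with an open list of confounders too, although baseline knowledge is not named. Such detail may lie in a full protocol or SAP that is not shown, so ANCOVA is an improvement here and not the repair of an error.
- **A reader might infer that the dependent t-tests ignore the baseline.** They are computed from pre-post differences, so they use it. What they would lack is the control arm, and the preceding sentence of the article supplies a between-arm test of knowledge.
- **The t-tests may not concern the women at all.** Under Education for midwives and dentists, it is midwives who "undertake the specific oral health education program endorsed by the Australian College of Midwives". Against this, the only pre-test and post-test of knowledge described in the article is the women's. The text does not settle it.
- **A reader might infer that the uptake effect will be diluted by adjusting for knowledge as a mediator.** The article does not say whether the pre-test or the post-test score would enter a model, and it names Pearson's chi-square, which has no covariates, for uptake. No size can be put on such a bias from this document.

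**Conclusion.** The point holds in a limited form. Naming a primary-hypothesis outcome score as a random effect is a stated error that conflicts with the same section's use of knowledge as an ANOVA outcome. It needs no assumption, and it should be corrected before analysis.

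The missing pre-test adjustment is a matter of efficiency. If post-test scores are what the ANOVA compares, ANCOVA would cut variance by 9%, 25% or 49% at r = 0.3, 0.5 or 0.7. The size depends wholly on that unknown correlation and on about 124 women per group completing both questionnaires. The dependent t-tests call for clarification only.

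**What to change.** - Delete knowledge as the example of a random effect. Enter no knowledge score measured after randomisation as a covariate in any model of the intervention effect.
- Analyse post-test knowledge by ANCOVA, with arm as a fixed effect, adjusted for baseline knowledge, hospital and dental-problem stratum, and with the planned pairwise contrasts.
- State which program, and whose scores, the dependent t-tests assess. If they concern the women, label them descriptive within-arm summaries that are not evidence of an intervention effect.

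The cost is a few sentences in the analysis section. The baseline scores and both strata are already collected, and the sample size does not change.
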